
### Participant timeline {13}

The participant timeline is shown in Fig. 1.

**Fig. 1 Fig1:**
[figure not shown]
Participant timeline. Abbreviations: Insomnia Severity Index (ISI), Pittsburgh Sleep Quality Index (PSQI), WHO-5 Well-Being Index (WHO-5)

### Sample size {14}

A power calculation was performed based on the results of a similar study [28] with PSQI as a secondary outcome using an average effect size of 0.67. Assuming a power of 0.80, a significance level of 0.05, and an expected power magnitude of 0.67, a sample size of *n* = 44 is obtained for each group. The expected 25% dropout rate is based on former experiences from a pilot project (*n* = 55). A total of 88 patients will be included in the study.

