Sleep problems are believed to play an important role in the onset, course, and treatment of UD, BD, and ADHD, with evidence suggesting a bidirectional relationship [6, 18–20]. Pharmacological sleep treatment is widespread but recommended for short-term use only due to the inherent risk of developing tolerance and addiction [21]. European and American guidelines recommend non-pharmacological treatment such as cognitive behavioral therapy for insomnia (CBT-I) as a first-choice treatment for chronic insomnia [21, 22]. CBT-I involves various interventions, including sleep restriction (limit time in bed to the actual sleep time); stimulus control method (strengthen the connection between bed and sleep); sleep hygiene education; relaxation training (reduce physiological arousal), and cognitive methods to address dysfunctional beliefs about sleep. CBT-I can be delivered in various treatment formats, including group, individual [23], and digital formats [24]. Meta-analyses found that CBT-I targeting insomnia with comorbid disorders had a medium to large effect on subjective sleep variables [25, 26].

The present intervention study is inspired by a transdiagnostic manual combining CBT-I with chronotherapy (treatment methods used to influence the circadian rhythm, such as bright light therapy and social rhythm therapy) in conjunction with motivational interviewing [27]. The manual provides transdiagnostic sleep interventions across a wide range of mental disorders [10]. Few studies have examined the effect of transdiagnostic sleep interventions. A positive effect on sleep parameters was shown in adolescents with various mental illnesses [28] and in 14 adolescents with ADHD [29]. Studies in adult outpatients with mental disorders and also midlife and older adults with serious mental illness documented a positive effect on sleep and circadian rhythm parameters and an improvement of psychiatric symptoms [30, 31]. However, despite extensive research on CBT-I, there is limited evidence of the effectiveness of combining CBT-I with chronotherapy as a transdiagnostic intervention in adult patients suffering from UD, BD, and ADHD. Therefore, more evidence is needed to adapt and incorporate the most effective interventions for sleep problems in mental healthcare services.

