### Trial design {8}

The study is a randomized controlled trial enrolling 88 outpatients with sleep problems (symptoms of chronic insomnia, circadian rhythm disorders, or hypersomnia) comorbid to BD, UD or ADHD. Patients are allocated to two parallel groups; an intervention group receiving six sessions of transdiagnostic sleep treatment or a control group receiving one session of sleep hygiene education. The allocation ratio is 1:1. After 6 weeks, the control group is offered the sleep intervention, but the data collected from this group will not be included in the present project.

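### The 44 per group does not follow from d = 0.67, 80% power and 25% dropout; 88 randomised gives about 76–78% power among completers (minor)

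*Protocol article*

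**What the plan says.** The section Sample size {14} takes its effect size from one cited study in which the PSQI was a secondary outcome, "using an average effect size of 0.67". It continues "Assuming a power of 0.80, a significance level of 0.05, and an expected power magnitude of 0.67" and gives 44 per group as the result. The next sentence reads "The expected 25% dropout rate is based on former experiences from a pilot project", and the paragraph ends with a total of 88. Trial design {8} adds "The allocation ratio is 1:1", so 88 is simply 2 × 44.

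The paragraph does not say whether the test is one- or two-sided, how many evaluable patients are required, or whether the 44 is the number before or after the dropout allowance.

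**The concern.** The order of the sentences presents 44 as the direct result of the power calculation, with dropout mentioned afterwards and no further inflation. Those inputs give a number well below 44, so dropout seems to be inside the 44 already. If so, the allowance looks too small for the rate named.

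This paragraph is the only justification of the trial's size. A null result on the PSQI would be read against the stated 80% power, so the reader should be able to see what 88 patients deliver after the dropout that the plan itself expects.

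**Working it through.** **Inputs.** From Sample size {14}: standardised difference d = 0.67, power 0.80, significance level 0.05, dropout 25%, 44 per group, 88 in total. From Trial design {8}: 1:1 allocation. Assumed: a two-sided test, because sidedness is not stated.

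**1. Evaluable patients needed.**
- Normal approximation: n = 2 × (1.96 + 0.8416)² / 0.67² = 2 × 7.849 / 0.4489 = 34.97, so 35 per group.
- t-test (noncentral t): 35.96, so 36 per group (power 0.8005 at 36).

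Neither is 44.

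**2. Reproducing the 44.**
- 35 × 1.25 = 43.75, rounded up to 44. This matches exactly.
- 36 × 1.25 = 45.
- One-sided at 0.05: 28 (normal) or 29 (t) evaluable. Multiplying by 1.25 gives 35 or 37; dividing by 0.75 gives 38 or 39. No one-sided variant gives 44.

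So the 44 is reproduced only as the two-sided normal-approximation figure with 25% added on top.

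**3. The allowance for a 25% loss.** If a quarter is lost, n / (1 − 0.25) must be randomised to keep n.
- 35 / 0.75 = 46.7, so 47 per group, 94 in total.
- 36 / 0.75 = 48 per group, 96 in total.

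The planned 88 is 6 to 8 patients fewer. Adding 25% on top covers a loss of only 1 − 1/1.25 = 20%.

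**4. What 88 delivers if 25% are lost.** 44 × 0.75 = 33 per group.
- Normal: 0.67 × √(33/2) − 1.96 = 2.722 − 1.96 = 0.762, so power is 77.7%.
- t-test: power is 76.4%.
- Effect detectable with 80% power: (1.96 + 0.8416) × √(2/33) = 0.69 (normal), or 0.70 (t-test).

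Within one method, the dropout step costs about 2.3 to 2.5 points: 80.0% at 35 against 77.7% at 33 (normal), or 78.9% against 76.4% (t-test). The rest of the distance from 80% to 76.4% is the difference between the two methods.

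**5. The other reading: 44 is the evaluable number.** Power at 44 per group is 87.4% (t-test) or 88.2% (normal), not 80%, and 2 × 44 = 88 randomised leaves no allowance for dropout.

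On neither reading do 44 per group, 80% power and a 25% dropout allowance hold together.

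**The case against.** The strongest reply is that a completers-only power figure does not describe the planned analysis. The statistical methods section specifies intention to treat with a maximum-likelihood linear mixed model, which uses partial data from patients who leave. This could restore the 80%. As an illustration, assume equal correlation ρ = 0.5 between visits, and that every dropout still supplies the PSQI at baseline and week 2. The share of week 6 variance explained by the two earlier visits is 2ρ²/(1 + ρ) = 0.5/1.5 = 1/3. The effective number per group at week 6 is then 1 / [(2/3)/33 + (1/3)/44] = 36, which gives about 81% power (normal) or 80% (t-test). With ρ = 0.3 the share is 0.18/1.3 = 0.138, and the effective number is 1 / [0.862/33 + 0.138/44] = 34.2, still short of 35. So this argument stands as a possibility. It depends on a correlation and a missingness pattern that the article does not give, and the sample size paragraph does not call on it.

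Dropout is also not the same as a missing PSQI. The sections on outcome collection {18a} and retention {18b} provide for asking patients who stop to complete the questionnaires, with PSQI and ISI first, and for completion by phone, at home or online. If 36 of 44 per group supply week 6 data (18% missing), the t-test has its 80%. This stands too: 33 per group is what remains if every dropout is without week 6 data.

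Sidedness is an assumption. A one-sided test at 0.05 would have about 85–86% power with 33 per group. But nothing in the article indicates a one-sided test, and no one-sided variant gives 44.

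A reader might also infer that 0.67 is unsuitable because the Background says of its source "A positive effect on sleep parameters was shown in adolescents with various mental illnesses [28", while this trial enrols adults. The documents do not support calling that an error. The population of the source is disclosed, and nothing in the article shows that the effect in adults would be smaller.

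**Conclusion.** The paragraph is wrong as written: the stated inputs give 35 or 36 evaluable patients per group, and the 44 contains a dropout allowance that is too small for the rate named. The error is minor. It amounts to 6 to 8 patients, or about 2 to 4 points of power: 76–78% in place of 80% at d = 0.67. This rests on a two-sided test, a 25% loss in each group and a comparison of completers only.

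A reader might infer that the trial is underpowered and must enrol more patients. The documents do not establish that, because the planned mixed model and the retrieval of questionnaires could narrow or close the gap. What they do establish is that the stated calculation does not yield the stated number.

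**What to change.** Restate the sample size paragraph so that it gives:
- the sidedness of the test;
- the evaluable number needed, 35 (normal approximation) or 36 (t-test) per group if two-sided;
- how dropout was applied to reach 44;
- what 88 randomised with 25% lost provides: 33 per group, about 76–78% power at d = 0.67 among completers, or 80% power at d of about 0.69 to 0.70.

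If the sponsor wishes to keep the claim of 80% on the strength of the mixed model, the paragraph should state the correlation between visits and the missingness pattern that support it.

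The cost is one corrected paragraph and a slightly less favourable power figure. Enrolment, conduct and analysis stay as they are.

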### Recruitment {15}

Patients are recruited among patients referred with sleep problems to “Psykiatriens Hus.” Patients may be referred to this intervention for sleep problems from several mental health outpatient clinics at Aarhus University Hospital, Psychiatry, and from two Municipal counseling services in Aarhus. Based on experiences from a previous pilot project, we expect 100 annual referrals of which approximately 50% will likely be included in the study. If the inclusion rate is unexpectedly low, the research team will visit the referring staff and advertise to boost participation in the project. If necessary, the expected 1.5–2-year duration of the enrolment period will be extended.

### Assignment of interventions: allocation

#### Sequence generation {16a}

All included patients will attend baseline assessments prior to randomization into the two study groups using block randomization with varying block sizes of 4, 6, and 8. Randomization will be set up in REDCap by an independent service provider.

#### Concealment mechanism {16b}

An investigator will be informed of allocation when pressing the randomization button in REDCap. However, detailed information on block size is not available.

#### Implementation {16c}

The investigator will inform the patients about their allocation and introduce them to either the intervention or the control group.

### Assignment of interventions: blinding

#### Who will be blinded {17a}

Blinding of allocation is not possible because of the nature of the intervention.

#### Procedure for unblinding if needed {17b}

Not applicable. Blinding is not possible because of the nature of the intervention. The data analysis will be performed blinded to the allocated intervention group.

### Data collection and management

#### Plans for assessment and collection of outcomes {18a}

Patients who discontinue study participation + / − 7 days from the planned follow-up at 2 or 6 weeks will be asked whether they wish to complete the questionnaires when they return the actigraph. The PSQI and ISI questionnaires will be prioritized.

#### Plans to promote participant retention and complete follow-up {18b}

Patients who deviate from intervention protocols due to, e.g., illness, are asked to complete the questionnaires as soon as possible. We offer to do this with the patients by phone, at a home visit or virtually based on the patient’s preference. We also allow a flexibility of + / − of 7 days from the planned follow-up visits.

#### Data management {19}

The following data will be collected:From the patients and their hospital records: name, phone number, personal identification number from the Danish Civil Registration System (“CPR number”), diagnosis, and medication prescriptions. The following additional data are included through a semi-structured assessment interview at inclusion: marital status, employment status, level of education, consumption of tobacco, alcohol, other drugs, previous treatment for sleep problems, and exposure to daylight are collected.From actigraphy (Actiwatch MotionWatch 8 from CamNtech Ltd, Cambrigde UK): SE, SOL, WASO, and NWAKE. The MotionWatch 8 is a wrist-worn activity monitoring device, similar in size to a watch, with a tri-axial accelerometer. It has a 4.0 Mbits of storage capacity and a waterproof casing. It is used to objectively monitor movement during sleep. For sleep scoring, a tri-axial accelerometer is used to monitor body movements. For differentiating between sleep and wake epochs, the MotionWare Software (version 1.2.28, CamNtech, Ltd.) is used. This device uses an algorithm that depends on thresholding, assigning an activity score to each epoch by totalizing the epoch in question and those surrounding it using weighting factors. If the activity score of an epoch is above a predefined threshold, the epoch is scored as wake; otherwise, it is scored as sleep. A 30-s epoch is used in this study. Patients are asked to wear the actigraph 24 h a day on their non-dominant wrist during the 6-week study. Patients are instructed to press the event-marker when they intend to sleep (“lights out”) and when they experience their final wake up in the morning. Sleep diaries are used to validate sleep and wake onset if the patients forget to press the eventmarker. The first author and an experienced sleep scientist will perform the scoring and analyze the actigraphic records. The degree of agreement between raters in ten scorings will be calculated and reported using the intraclass correlation coefficient.From sleep diaries: The use of sleep medication “as needed”, bedtime (“lights out”), sleep onset, wakeup time and time for getting out of bed, SE, SOL, WASO, NWAKE, daytime naps including lengths (Additional files 2 and 3: Sleep and medication diary for the intervention and control group).From six validated questionnaires:The ISI measures the subjective experience of insomnia severity. The scale ranges from 0 to 28. The higher the score, the more severe the insomnia [38].The PSQI measures sleep quality [37]. The score ranges from 0 to 21, “0” indicating no difficulty and “21” indicating severe difficulties.The WHO-5 describes well-being (38). The questionnaire measures well-being on a scale ranging from 0 to 100. The higher the score, the more well-being.The INSPIRE-O consists of five short questions that measure personal recovery [40]. The questionnaire measures personal recovery on a scale ranging from 5 to 25. The higher the score, the more recovery.The Work Ability Index, a questionnaire measuring work ability [41]. A score of 0 shows the lowest possibility that the person would take on a job; a score of 10 denotes the highest probability.The International EQ-5D-5L questionnaire estimates quality-adjusted years of life. The questionnaire is applied to estimate quality-adjusted years of life [42].

All patients complete the six validated questionnaires at personal visits at baseline (week 0) and again after 2 and 6 weeks. Patients are asked to wear actigraphs around the clock during all 6 weeks and to complete a short sleep diary on a daily basis (see Additional files 2 and 3). Furthermore, they complete the morningness-eveningness questionnaire (MEQ) at week 2 to estimate their chronotype. This validated questionnaire has scores ranging from 16 to 86. Scores of 41 and below indicate “evening types.” Scores of 59 and above indicate “morning types.” Scores between 42 and 58 indicate “intermediate types” [43]. For the study schedule used for enrolment, intervention, and assessments, please see Table 1.

**Table 1 Tab1:**
[figure not shown]
Study schedule used to record enrolment, intervention, and assessment

All data will be stored in REDCap; a secure browser-based, metadata-driven EDC software solution and workflow methodology to design clinical and research databases [44].

### Confidentiality {27}

Data will be entered and securely stored in REDCap. Data will be fully anonymized before being shared with co-authors and the statistician at the Department of Affective Disorders at Aarhus University Hospital, Denmark. The trial will be conducted in conformity with the Declaration of Helsinki—Ethical principles for medical research involving human subjects.

### Plans for collection, laboratory evaluation, and storage of biological specimens for genetic or molecular analysis in this trial/future use {33}

Not applicable, no samples will be collected.

### Statistical methods

#### Statistical methods for primary and secondary outcomes {20a}

Demographic and clinical data used to compare the intervention and control group will be analyzed using descriptive statistics. Categorical variables will be reported using proportions, whereas means and standard deviations will be reported for continuous variables. Fisher’s exact test and Student’s *t*-test are applied to test for the difference between the intervention and control group for categorical and continuous variables. The intent-to-treat method will be used to examine if a significant change in the ISI and PSQI total scores from baseline to 6 weeks can be established.

To compare the differences in measurements between the intervention and control group over time, we will apply a linear mixed effects (LME) model, which is recommended for longitudinal data with missingness [45]. The “maximum likelihood estimation” assuming “missing at random” for data is used to examine the primary and secondary continuous objectives. The fixed components of the model are gender, age, time variable (1: baseline, 2: 2 weeks, 3: 6 weeks), type of treatment (1: intervention group, 2: control group), and the interaction between the time variable and the type of treatment. Means, standard deviation, 95% confidence interval, power magnitude, and the average reduction over time and *p*-value for reduction in the primary and secondary outcomes will be calculated from the model. All statistical analyses will be performed using Stata version 15., R-Studio, or SPSS version 20.0.

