### Outcomes {12}

#### Primary outcome

Changes in the quality of sleep measured by the Pittsburgh Sleep Quality Index (PSQI) [37].

Data are obtained by questionnaires at inclusion (baseline/week 0), at week 2, and at week 6.

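### The planned mixed model leaves baseline means free by arm; a shared baseline mean or a baseline covariate would gain precision at no cost (an improvement, not an error)

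*Protocol article*

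**What the plan says.** Statistical methods {20a} lists the fixed part of the linear mixed model for the primary and secondary continuous outcomes. It begins "The fixed components of the model are gender, age, time variable". The time variable is coded "time variable (1: baseline, 2: 2 weeks, 3: 6 weeks", so baseline PSQI is a response and not a covariate. The list ends with "type of treatment (1: intervention group, 2: control group), and the interaction between the time variable and the type of treatment". It contains no baseline score as a covariate and no constraint to a common baseline mean.

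On what will be reported, the same section says that "the average reduction over time and *p*-value for reduction in the primary and secondary outcomes will be calculated from the model". It does not name a between-arm contrast at week 6 as the treatment effect. Because the section's aim is to compare the arms over time, the week 6 interaction is the natural reading.

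Sequence generation {16a} fixes the timing of baseline: "All included patients will attend baseline assessments prior to randomization into the two study groups".

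**The concern.** Baseline comes before randomisation, so the true arm means at baseline are equal by design and any observed difference is chance. A model with a free baseline mean per arm subtracts that chance difference in full. An efficient analysis subtracts only the part that baseline predicts at follow-up. The plan adjusts for age and gender but does not make efficient use of baseline PSQI, which is usually the strongest predictor of later PSQI.

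What is at stake is precision on the primary outcome and on the other questionnaire outcomes measured at the same three visits, in a trial of 44 patients per arm. Validity is not at stake.

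**Working it through.** **The plan's own figure.** Sample size {14} works "using an average effect size of 0.67", with power 0.80 and a significance level of 0.05. Taken as two-sided, the normal approximation gives 35 per arm. 35 × 1.25 = 43.75, which rounds up to 44 per arm and 88 in total, so the stated figure is reproduced. No correlation or SD enters it, and the article does not say which SD standardises 0.67.

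**Inputs.** From the article: 44 per arm, 25% expected dropout (11 of 44 per arm), three visits, and the model terms above. Assumed, because not given: a baseline to week 6 correlation r of 0.3 to 0.8, and a ratio k of week 6 SD to baseline SD of 1.0 to 1.5.

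**Step 1: what the model estimates.** The stated model (age, gender, time, treatment, interaction, random intercept, maximum likelihood) was fitted to simulated data with 44 per arm.
- Complete data: week 6 interaction −1.4877; raw change-score difference −1.4877. They are identical.
- A second data set with 11 per arm missing at week 6: interaction −1.427; raw completer change difference −1.574. They are close but no longer equal, because the model also uses the incomplete patients.

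**Step 2: variance per patient.** With baseline SD s0 and week 6 SD s6:
- change score: s0² + s6² − 2·r·s0·s6
- baseline-adjusted: s6²·(1 − r²)
- difference: (s0 − r·s6)², which is never negative and is zero when r·k = 1

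With equal SDs of 1 these become 2(1 − r) and 1 − r², so the ratio of adjusted to change-score variance is (1 + r)/2.

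**Step 3: dropout.** The variance of the week 6 contrast was computed by generalised least squares with a free and with a common baseline mean. The calculation used equal SDs, the same correlation r between all visits, and 11 per arm missing week 6 (all leaving either before or after week 2).

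| r | 2(1 − r) | 1 − r² | Cut, complete data | Cut, 25% missing at week 6 | Cut, complete data, k = 1.25 |
|---|---|---|---|---|---|
| 0.3 | 1.40 | 0.91 | 35% | 29% | 22% |
| 0.4 | 1.20 | 0.84 | 30% | 24–25% | 16% |
| 0.5 | 1.00 | 0.75 | 25% | 20% | 11% |
| 0.6 | 0.80 | 0.64 | 20% | 16% | 6% |
| 0.7 | 0.60 | 0.51 | 15% | 12% | 2% |
| 0.8 | 0.40 | 0.36 | 10% | 8% | 0% |

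At k = 1.5 the cut with complete data is between 0.2% and 13% over the same correlations.

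**Step 4: what this means for power, in one case.** Take r = 0.5 with equal SDs. The SD of change is then √(2 × 0.5) = 1, so it does not matter which SD standardises 0.67. With 25% missing, the variance of the contrast in the stated model is 0.0556 to 0.0568. This gives 0.67/√0.0556 = 2.84 to 0.67/√0.0568 = 2.81, and power of about 0.80 to 0.81. With a common baseline mean the variance is 0.0442 to 0.0455, the ratios are 3.19 to 3.14, and power is about 0.88 to 0.89.

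**The case against.** The strongest reply is that nothing here is wrong. A mixed model with baseline as a response and time, treatment and their interaction is a standard trial analysis. It fits an outcome defined as change, and its contrast is unbiased under randomisation. That stands in full. A reader might infer that the plan is biased or invalid, but the documents do not support that.

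Other stronger readings also fail:

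- **A fixed gain of 20–25%.** This is only the case of r about 0.5 to 0.6 with equal SDs and complete data. The article gives neither quantity. A wider spread at week 6 is plausible, since Eligibility criteria {10} requires ISI of at least 14 and so may narrow the range at baseline. That would shrink the gain.
- **A raw change-score analysis.** The identity is exact only with complete data. With the expected dropout, maximum likelihood departs from it.
- **A trial already short of its stated power because of this model.** In the case worked above, the stated model with 25% missing still has power of about 0.80. With other correlations the answer depends on which SD standardises 0.67, and the article does not say.
- **An inflated type I error from maximum likelihood.** The article does say that "The “maximum likelihood estimation” assuming “missing at random” for data is used to examine the primary and secondary continuous objectives". Any inflation depends on the reference distribution and degrees of freedom, which it does not name and which a statistical analysis plan commonly fixes.

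The criticism that survives is that the listed fixed effects are complete enough to settle how baseline is used, and they settle it inefficiently when a better option is free.

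**Conclusion.** The point holds as a recommendation. The stated model is valid but does not use the fact, fixed by the trial's own design, that both arms have the same expected baseline.

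The size is uncertain and should be quoted as a range: about 35% to 10% less variance for r = 0.3 to 0.8 with complete data, or about 29% to 8% with a quarter of week 6 values missing. Both ranges assume equal SDs at baseline and week 6, and the second also assumes equal correlation between visits. If the week 6 SD is larger than the baseline SD, the gain is smaller and can be about nil. In large samples the efficient analysis is never less precise, so the change carries little risk even where the gain is small.

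**What to change.** Change the model wording in one of two ways:

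- **Common baseline mean (constrained longitudinal model).** Keep baseline as a response, drop the treatment main effect, and use time, treatment × week 2, treatment × week 6, age and gender as fixed effects.
- **Baseline as covariate.** Model weeks 2 and 6 only, with time, treatment, treatment × time, baseline value × time, age and gender.

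In either case, name the week 6 between-arm contrast, with its confidence interval, as the primary treatment effect. Apply the same model to ISI, WHO-5, INSPIRE-O and the Work Ability Index. Fitting by REML with a small-sample degrees-of-freedom method is an optional minor refinement.

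The cost is wording only: no extra patients, visits or data. The first option uses one parameter fewer than the stated model. The choice should be fixed before the analyst sees outcome data by arm.
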